#### Secondary analysis

A generalized estimated equations (GEE) analysis will be conducted to determine whether there is an effect of treatment arm over time (repeated measures) on the MEPS outcome, considering measures taken preoperatively, and at 3, 6, 12 and 24 month follow-ups. Other secondary analyses involves a comparison of the secondary outcome measures between the two surgical treatment groups. Differences in the mean abbreviated DASH and ASES-e scores, as well as grip strength, will be tested with ANOVAs and effect sizes estimated with linear regression. Median time back to work in each group will be derived with Kaplan-Meier survival curves, and a statistical comparison between groups will be tested using a log rank test.

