## Methods

### Study design

This study is designed as a prospective single center, double-blind, randomized sham-controlled parallel arm trial, stratified on the need for debridement. After diagnostic arthroscopy, patients will be randomly assigned to ATER or sham (i.e. placebo) surgery and stratified by whether they require debridement or not. The study is designed to abide by the current international research standards and will be reported according to the guidelines listed in the CONSORT statement [27]. The study is approved by the Ottawa Health Science Network Research Ethics Board of Ottawa, Canada and is in compliance with the Tri-Council Policy Statement: Ethical Conduct for Research Involving Humans; the International Conference on Harmonization – Good Clinical Practice: Consolidated Guideline and the provisions of the Personal Health Information Protection Act 2004.

The surgeries will be performed by a single fellowship-trained upper extremity orthopaedic surgeon with at least seven years of independent practice experience at a university-affiliated academic center.

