### Purpose and hypothesis

The purpose of the study is to determine whether ATER is superior to non-operative management using a sham surgery control group for the management of chronic lateral epicondylitis of the elbow at 24 months postoperative as measured by the Mayo Elbow Performance Score (MEPS). Data will be collected at baseline and at 3, 6, 12 and 24 months following surgery. In addition, we will aim to determine if there is a differential effect of ATER versus sham surgery among the subgroup of patients requiring additional elbow debridement due to coexisting intra-articular pathology. Furthermore, we will compare the effect of ATER and sham surgery on the abbreviated DASH and American Shoulder and Elbow Surgeons Elbow (ASES-e) scores at the different timepoints, as well as assess for any differences in grip strength, return to work time and adverse outcomes between the two groups.

We hypothesize that at 24 months, the improvement in MEPS is greater after ATER than sham surgery. Furthermore, we hypothesize that the DASH, ASES-e will also favor ATER at all postoperative timepoints. In addition, we hypothesize that grip strength will be diminished in the ATER group compared to sham, but that return to work time will favor ATER Table 1.

**Table 1 Tab1:** Data collection timeline

Variable	Baseline^a^Preoperative	T = 2 weeks Postoperative	T = 6 weeks Postoperative	T = 3 months Postoperative	T = 6 months Postoperative	T = 1 year^b^Postoperative	T = 2 years Postoperative
*Patient demographics*							
Age (years)	X						
Sex (M/F)	X						
Duration of symptoms (months)	X						
Arm affected (L/R)	X						
Dominant arm (L/R)	X						
Height (cm)	X						
Weight (kg)	X						
Body-Mass Index (BMI)	X						
Occupation	X						
Smoker (Y/N)	X						
Diabetic (Y/N)	X						
*Outcome measure*							
MEPS^c^	X			X	X	X	X
*Quick*DASH	X			X	X	X	X
ASES-e	X			X	X	X	X
Grip strength (grip dynamometer)	X			X	X	X	X
Return to work (Y/N)				X	X	X	X
Complications		X	X	X	X	X	X

^a^Second clinical visit

^b^Primary endpoint

^c^Primary outcome measure

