### Participants

Patients eligible for inclusion in the study will be aged >18 years and have had symptoms for at least 6 months and have subsequently failed a 3-month course of conservative management consisting of activity modification, anti-inflammatories, physiotherapy, corticosteroid and platelet-rich plasma injections. Patients with an alternative diagnosis that better explains their symptoms or those who have had significant prior elbow trauma or surgery are not eligible to be a part of the trial. Workplace Safety and Insurance Board (WSIB) patients (workplace injuries) are also excluded from the study. Patients must be able to speak English. General Practitioners in the Ottawa area will be sent a letter asking them to refer patients who meet the eligibility criteria listed above. Eligible patients will receive informed consent on the two treatment arms. Enrolled participants will undergo a functional outcome scores assessment (MEPS, abbreviated DASH, ASES-e, grip strength) at the second preoperative clinical visit, which will serve as a baseline for comparison. They will then be scheduled for surgery through the standard outpatient surgery program.

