### Statistical considerations

#### Primary analysis

The primary analysis involves a comparison of the MEPS outcome measure between the two surgical treatment groups on an intention-to-treat basis at 24 months post-surgery as compared to baseline values. A two-sample independent ANCOVA will be used to assess whether there is a statistically significant difference between groups for the MEPS scores, accounting for the debridement stratification variable and baseline MEPS. Linear regression will be used to estimate treatment size effect, accounting for the stratification variable and baseline MEPS, as well as any possible imbalanced covariates. Primary analyses will be repeated for the debridement and no-debridement patient subgroups. Missing follow-up data will be addressed with multiple imputation techniques.

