#### Sample size calculation

The primary outcome is the modified Mayo Elbow Performance score. A minimum clinically importance difference of 15 points has been derived for patients with rheumatoid arthritis [31]. In a study of patients with elbow dysfunction, standard deviations ranged from 17 to 19 points [28]. In order to attain a study power of 80 % to detect a minimally clinically important difference of 15 points on the MEPS primary outcome measure at one year follow-up using ANOVA to compare ATER versus sham, and assuming a standard deviation of 19 points as well as an alpha level of 0.05, a total sample size of 52 patients will be required (group sizes of 26) [31, 32]. However, adjusting for the remote possibility of 5 % of patients requiring un-blinding in the case of sham surgery (drop out), and a possible 15 % loss to follow-up yields a total sample size of 68 (34 in each group).

Assuming a recruitment and consent rate of 70 %, we would need to approach 97 patients to achieve our required sample size. Hospital records indicate that our clinic sees approximately 10 eligible patients per month, meaning we can feasibly achieve our required sample size within 10 months of enrollment.

Patients who are excluded from the trial intra-operatively and patients whose symptoms resolve prior to intra-operative randomization will only be followed clinically and not as part of this study.

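### The secondary GEE on MEPS lists the pre-randomisation score as a repeated outcome; unless the arms share a common baseline mean, it loses precision that adjusting for baseline would keep

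*Protocol article*

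**What the plan says.** The protocol article, under Secondary analysis, plans a GEE for the "effect of treatment arm over time (repeated measures) on the MEPS outcome, considering measures taken preoperatively, and at 3, 6, 12 and 24 month follow-ups". The preoperative score thus stands in one list with the four follow-up scores. The sentence does not give the model terms, the contrast tested, or any constraint on the arm means at baseline.

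That score is collected "at the second preoperative clinical visit, which will serve as a baseline for comparison" (Participants). Allocation comes later, in the operating room: "After diagnostic arthroscopy, patients will be randomly assigned to ATER or sham" (Study design).

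For the same outcome, Primary analysis specifies an ANCOVA "accounting for the debridement stratification variable and baseline MEPS". The baseline is therefore a covariate in one MEPS analysis and one of the repeated measures in the other.

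**The concern.** A score recorded before randomisation cannot carry a treatment effect. If it enters as an ordinary outcome occasion, one of two things follows under the usual parameterisations.

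- **Arm-by-time terms, arms free at baseline.** The model estimates a baseline arm difference whose expected value randomisation already fixes at zero. The sampling noise in that estimate passes into every post-operative contrast.
- **One arm term over all occasions.** The estimate averages in a visit with no effect and is pulled towards zero.

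This is the only planned analysis that uses all MEPS visits together, in a trial sized at 52 evaluable patients, so avoidable loss of precision matters. Readers would also see the baseline handled in two ways for one outcome. If the two analyses differed, they could not easily tell how much was due to the data and how much to the model.

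**Working it through.** **Inputs.** Sample size calculation gives the target as "to detect a minimally clinically important difference of 15 points on the MEPS primary outcome measure at one year follow-up", "assuming a standard deviation of 19 points as well as an alpha level of 0.05", with 80% power and 26 evaluable patients per group. Two-sided testing is assumed. The within-patient correlation ρ is not in the document, so 0.3, 0.5 and 0.7 are assumed, with compound symmetry and complete data. The 15 points are also applied at 24 months, the time point named in Primary analysis. Under compound symmetry the single-visit results are the same at any post-operative visit.

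**The plan's own figure.** n per arm = 2 × (1.960 + 0.842)² × 19² / 15² = 25.2, rounded up to 26, or 52 in total. This reproduces the stated number. No power is stated for the GEE.

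**Per-patient variances, in units of σ² = 361.**

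- Raw change at one visit: 2(1 − ρ). Baseline-adjusted: 1 − ρ². Ratio 2/(1 + ρ) = 1.54, 1.33, 1.18.
- Average of four post-operative visits minus baseline: (1 + 3ρ)/4 + 1 − 2ρ = 1.25(1 − ρ). Baseline-adjusted: (1 + 3ρ)/4 − ρ² = (1 − ρ)(1 + 4ρ)/4. Ratio 5/(1 + 4ρ) = 2.27, 1.67, 1.32.
- One arm term over five occasions: variance (1 + 4ρ)/5. Expected value for a constant effect: (0 + 4 × 15)/5 = 12.

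**Power.** SE = √(2 × variance / 26), and power ≈ Φ(effect/SE − 1.96). At ρ = 0.3:

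- 24 months, raw change: SE = √(2 × 505.4 / 26) = 6.24; 15/6.24 = 2.41; power 67%.
- 24 months, adjusted: SE = √(2 × 328.5 / 26) = 5.03; 15/5.03 = 2.98; power 85%.
- Average, raw change: SE = √(2 × 315.9 / 26) = 4.93; 15/4.93 = 3.04; power 86%.
- Average, adjusted: SE = √(2 × 139.0 / 26) = 3.27; 15/3.27 = 4.59; power >99%.
- Five-occasion arm term: SE = √(2 × 158.8 / 26) = 3.50; 12/3.50 = 3.43; power 93%.

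| 15 points, 26 per arm | ρ = 0.3 | ρ = 0.5 | ρ = 0.7 |
|---|---|---|---|
| 24 months, raw change | 67% | 81% | 96% |
| 24 months, baseline-adjusted | 85% | 91% | 98% |
| Post-operative average, raw change (constant effect) | 86% | 95% | >99% |
| Post-operative average, baseline-adjusted | >99% | >99% | >99% |
| Five-occasion arm term (expects 12) | 93% | 84% | 74% |

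**Check with fitted GEEs.** Exchangeable GEEs with robust standard errors were simulated with a constant 10-point effect (600 runs per ρ). Power at ρ = 0.3/0.5/0.7:

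- five-occasion arm term: 68/52/41%, with mean estimates near 8;
- change contrast with arms free at baseline: 55/69/89%;
- common baseline mean: 87/88/96%;
- baseline as covariate: 86/87/95%.

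The last two agree, so keeping the baseline as an outcome costs nothing once the arms share its mean.

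**Effect that builds up.** With effects of 0, 5, 10 and 15 points at the four visits, the joint 4-df arm-by-visit test has 65/81/97% power, against 79/88/98% with a common baseline mean. For a constant 15 points the figures are 68/84/98% against 97/98/>99%. The loss on that joint test therefore shrinks when the effect builds gradually. The 24-month contrast does not depend on the earlier visits, and the variance ratios do not depend on the effect profile. For the post-operative average, which is then 7.5 points, power is 33/44/64% against 63/64/76%, so the loss there does not shrink.

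**The case against.** The strongest reply is that the article does not fix the model criticised here. A GEE with the preoperative score in the outcome vector and a common baseline mean satisfies the sentence word for word and loses nothing, and such detail is often left to an analysis plan. This stands in part: the loss does not follow from the text alone. But the sentence does place a pre-randomisation score among the repeated measures, and a plain arm, time and arm-by-time model fitted to that list produces the loss. The covariate wording used for the primary analysis is absent.

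A second reply is that the hypothesis concerns improvement: "We hypothesize that at 24 months, the improvement in MEPS is greater after ATER than sham surgery". A change contrast estimates that directly and without bias. This is true, but under randomisation the baseline-adjusted contrast has the same expected value and a smaller variance.

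A reader might infer more than the document supports:

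- **That the GEE estimate is biased towards zero.** This holds only if one arm term spans all five occasions. An effect of arm over time reads more naturally as arm-by-time, where nothing is diluted.
- **That the GEE would miss real effects, with a loss of about 33 percentage points.** That size (62% against 95%, by simulation with small-sample tests) belongs to a 4-df joint test at ρ = 0.3 with a constant effect. It is not a general figure.
- **That the GEE is less sensitive than the single-visit ANCOVA.** Under compound symmetry the averaged change contrast has variance 1.25(1 − ρ) against 1 − ρ², so it is the more precise of the two whenever ρ exceeds 0.25. The GEE falls behind when its own 24-month change contrast is set against the 24-month ANCOVA.

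**Conclusion.** The point holds as a loss of precision in a secondary analysis, conditional on the arms not being constrained to a common baseline mean. Under the more natural arm-by-time reading the estimate is valid, with variance 1.54/1.33/1.18 times the adjusted one at 24 months and 2.27/1.67/1.32 times for the post-operative average, at ρ = 0.3/0.5/0.7. For 15 points at 24 months this costs about 18, 10 and 2 percentage points of power. For a constant effect averaged over visits it costs about 13, 5 and almost none. Dilution from 15 to 12 points applies only under the less likely single-arm-term reading.

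These sizes rest on an assumed ρ, compound symmetry, SD 19, 26 evaluable patients per arm and large-sample tests. Type I error is unaffected: simulated rejection rates with no effect were 4.7% to 5.1% at ρ = 0.3 and 0.5. The primary ANCOVA and the sample size are untouched.

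**What to change.** In Secondary analysis, state that the GEE outcomes are MEPS at 3, 6, 12 and 24 months, with preoperative MEPS and debridement stratum as covariates and visit as a categorical factor. Alternatively, keep the preoperative score as an outcome and state that the two arms share a common baseline mean. In either case, name the contrasts to be reported: the average post-operative arm effect and the arm effect at each visit.

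This takes a sentence or two. It needs no new data or patients, because the baseline score and the stratum are already collected, and it brings the GEE into line with the primary ANCOVA.

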**Methods:**

We will conduct a prospective single center, double-blind, randomized sham-controlled parallel arm trial evaluating the efficacy of arthroscopic tennis elbow release in adult patients with symptoms for at least 6 months. Patients will undergo intraoperative randomization after diagnostic arthroscopy of the elbow to receive either ECRB release (through the creation of a lateral portal) or a sham lateral portal and no ECRB release. The primary outcome will be the Mayo Elbow Performance Score (MEPS) at 1 year follow-up. Secondary outcomes will be the abbreviated Disability of the Shoulder and Hand (DASH) score, American Shoulder and Elbow Surgeons elbow (ASES-e) score and grip strength at 3, 6, 12 and 24 months as well as return-to-work time, ability to return to full duty and adverse outcomes.

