### Postoperative protocol

Post-operative follow-up is at 2 weeks, 6 weeks, 3, 6, 12 and 24 months. Functional outcome scores will be obtained from each patient at the 3, 6, 12 and 24 month time points. Post-operative management will be identical among the two treatment arms and consists of immediate elbow range of motion exercises and no weight-bearing restrictions. However, elbow, forearm and shoulder strengthening exercises will begin at 10 weeks postoperative. Patients (independent of concealed group allocation) will receive functional counseling by a licenced physiotherapist at the first postoperative visit and will be provided with a standardized exercise protocol to guide outpatient physiotherapy.

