#### ASES-e

The ASES-e score is both patient and physician-administered. The patient-reported self-evaluation consists of pain, function and satisfaction components. The pain component utilizes the visual analogue scale (0 to 10, with 10 indicating the worst pain ever), while the function component pertains to the patient’s ability to perform specific upper extremity-related tasks (0 to 4, with 4 indicating no difficulty). Satisfaction is graded 0 to 10. The physician assessment consists of motion, strength (both in flexion, extension, pro-supination), stability (varus, valgus, posterolateral rotatory) and physical findings (tenderness, scars, etc). Stability is graded 0 to 3, with 3 grading gross instability, while strength is graded 0 to 5, with 5 indicating normal strength. Physical findings are reported as being present or not.

The MEPS, DASH and ASES-e scores are all validated, upper extremity-specific questionnaires [29]. We will also be testing grip strength using a standard grip dynamometer and compare return to work time and adverse outcomes between the two groups.

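### Time to return to work is to be analysed by Kaplan-Meier and log-rank, but Table 1 records only a yes/no at 3, 6, 12 and 24 months, so the median can only fall on a visit and the test loses power

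*Protocol article*

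**What the plan says.** The Abstract (Methods) lists among the secondary outcomes "return-to-work time, ability to return to full duty and adverse outcomes". Purpose and hypothesis predicts that "return to work time will favor ATER", and the end of the Secondary outcomes section says the trial will "compare return to work time and adverse outcomes between the two groups". The Secondary analysis section fixes the method: "Median time back to work in each group will be derived with Kaplan-Meier survival curves". For the comparison of the arms it names the log-rank test.

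The data come from Table 1, the data collection timeline. Its only return-to-work row begins "Return to work (Y/N", that is, a yes/no item. It is marked at 3 months, 6 months, 1 year and 2 years. The Postoperative protocol section has earlier visits too ("Post-operative follow-up is at 2 weeks, 6 weeks, 3, 6, 12 and 24 months"), but at 2 and 6 weeks Table 1 marks only complications. The article nowhere mentions a date of return, a count of days off work, or a method for interval-censored data.

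**The concern.** The analysis and the data are of different kinds. A Kaplan-Meier median in weeks or days needs to know when each patient went back to work. A yes/no at four widely spaced visits says only between which two visits it happened, and the first interval covers the whole of the first 3 months.

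That interval may hold much of the information. After surgery patients have "immediate elbow range of motion exercises and no weight-bearing restrictions", so return within 3 months is plausible for many of them. Every such patient would be entered as an event at 3 months, whether the return came in week 1 or week 12. At stake are the estimate of a named secondary outcome and the power to test a directional hypothesis stated in advance.

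**Working it through.** **Inputs from the article.** Yes/no at 3, 6, 12 and 24 months (Table 1). Kaplan-Meier median and log-rank test (Secondary analysis). 34 patients per arm enrolled, after allowances of 5% and 15% for losses (Sample size calculation).

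**The plan's own figure.** No median, event count or power is stated for return to work. The only computed figure is the MEPS sample size: n per arm = 2(1.96 + 0.84)² × 19²/15² = 2 × 7.85 × 1.604 = 25.2, rounded up to 26, or 52 in total, as stated. The present point does not depend on it; only the 34 per arm is carried forward.

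**Step 1: what the visit data allow.** Each return is known to lie in (0, 3], (3, 6], (6, 12] or (12, 24] months, or not to have occurred by 24 months. If the event is dated to the first visit with a yes, the Kaplan-Meier curve steps only at 3, 6, 12 and 24 months, so the median is one of those values or is not reached. With no earlier censoring, S(3 months) = 1 − d/n, where d is the number back by 3 months. The median is therefore 3 months once d/n ≥ 0.5, which is 17 or more of 34. If this holds in both arms, both medians read 3 months. This step needs no assumption about effect size.

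**Step 2: overstatement.** Three months is 3 × 52.18/12 = 13.05 weeks. True medians of 4 and 8 weeks would both be reported as about 13 weeks, which is about 9 and 5 weeks too long, and the 4-week difference would be reported as zero.

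**Step 3: what the log-rank test still sees.** For an exponential time with median m weeks, the proportion back by 3 months is 1 − 2^(−13.05/m). For m = 4 this is 1 − 2^(−3.26) = 0.90; for m = 8 it is 1 − 2^(−1.63) = 0.68. The gap of 0.22 still reaches the test. For m = 2 against 4 it is 0.99 against 0.90, a gap of only 0.09.

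**Step 4: power.** The article gives no return-to-work times, so the true medians are assumed: exponential times, hazard ratio 2, 34 per arm all working before surgery, no dropout, two-sided 5% test, 1,500 simulated trials per row.

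| True medians, ATER v sham (weeks) | Back by 3 months | Power, dates | Power, visit data | Both medians on the same visit |
|---|---|---|---|---|
| 2 v 4 | 0.99 v 0.90 | 0.80 | 0.36 | 100% |
| 3 v 6 | 0.95 v 0.78 | 0.78 | 0.61 | 100% |
| 4 v 8 | 0.90 v 0.68 | 0.79 | 0.70 | 99% |
| 6 v 12 | 0.78 v 0.53 | 0.78 | 0.73 | 69% |
| 8 v 16 | 0.68 v 0.43 | 0.80 | 0.75 | about 23% |
| 13 v 26 | 0.50 v 0.29 | 0.79 | 0.75 | about 24% |

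The simulation error of a power near 0.37 is √(0.37 × 0.63/1,500) ≈ 0.012. A repeat with other random numbers gave 0.79 v 0.37, 0.80 v 0.70 and 0.79 v 0.76 for the 2 v 4, 4 v 8 and 13 v 26 rows, which agrees within that error. With no true difference, the log-rank test on visit data rejected in about 5% of runs.

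**Sensitivity.** With 27 per arm (68 × 0.80 = 54.4 in total after losses), 2 v 4 weeks gives 0.68 v 0.23 and 13 v 26 weeks gives 0.67 v 0.62. With a Weibull shape of 2 instead of exponential times (1,000 runs, 34 per arm), 4 v 8 weeks gives over 0.99 with dates and 0.82 with visit data.

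**The case against.** The strongest reply is that this is a condensed journal article. It speaks of return-to-work time in several places, Table 1 shows when items are asked rather than how each form field looks, and a date may well be written down beside a yes. That is a fair limit. The defect is therefore stated conditionally: it applies if the yes/no is all that is recorded. It does not remove the point, because Table 1 is the collection schedule the article gives, it labels the item yes/no, and no other text says a date is taken.

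Two stronger conclusions are tempting, and neither is supported. A reader might infer that early differences become invisible. They do not: the test still sees them through the proportion back at work by 3 months, and in most of the scenarios above it keeps most of its power. A reader might also infer that the medians would be equal even if one arm returned twice as fast. That holds only when both medians fall in the same visit interval. At 13 v 26 weeks it happens in only about a quarter of trials. Strengthening exercises start at 10 weeks (Postoperative protocol), so medians near 3 months cannot be ruled out.

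Nor is the log-rank test invalid. Both arms share the same visit grid, and its type I error stays near 5%.

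Finally, full duty has no row in Table 1 and baseline work status is not listed (occupation is). For an article these are mainly missing detail, and they are not part of the point.

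**Conclusion.** The mismatch is real. Followed as written, the plan cannot give a Kaplan-Meier median other than a visit time, that median overstates the true time, and it cannot separate the arms when at least half of each is back by 3 months. That much follows from the schedule alone.

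The loss of log-rank power depends on when patients actually return. Under assumed twofold differences and exponential times it runs from about 3 to 5 points when medians lie near or beyond 3 months to over 40 points when they are 2 and 4 weeks. The article gives nothing with which to choose within that range. The comparison is weakened, not invalidated.

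The outcome is secondary, the sample size was not set for it, and the primary MEPS conclusion is untouched. The change is still worth making before patients are seen, because early dates not captured at the time can be recovered only by long recall.

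**What to change.** Change the return-to-work row of Table 1 to record the date of first return to work, and ask for it at every existing visit, including 2 and 6 weeks. Run the planned Kaplan-Meier median and log-rank test on those dates in patients who were working before surgery. If the case report form already takes a date, correcting the row label and saying so is enough.

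If only the yes/no is kept, replace the median and log-rank test with an interval-censored or discrete-time analysis, or compare the proportions back at work at each visit. Any of these matches the method to the data, but none recovers the timing within the first 3 months.

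The cost is one extra field on existing forms at existing visits, and a small recall error in self-reported dates.

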### Randomization

The patients will be brought to the operating room where they will undergo a regional block anesthetic. A diagnostic arthroscopic evaluation will then be performed through a medial portal. Following this, the surgeon will make a decision as to whether the elbow requires any debridement. The decision to debride is a clinical one and is influenced by the presence of an intra-articular pathology, such as extensive synovitis (inflammation), loose bodies and radiocapitellar plicae. Patients who are deemed to require intra-articular debridement will receive it at this point. This requires the creation of a lateral, working portal. Patients who do not require debridement will be randomized to ATER or sham. Similarly, patients who do require debridement will be randomized to ATER or sham.

A randomization sequence will be computer generated by an independent statistician. Consecutive patients will be randomized to receive ATER or Sham surgery in a 1:1 allocation ratio, with stratification by the need for debridement and randomly permuted block sizes from 2, 4, or 6. Central randomization will be accomplished by the use of online registration and verification of eligibility through the Data Management Services group at the Ottawa Hospital Research Institute Fig. 1.

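### The return-to-work log-rank test names no stratum although randomisation is stratified by debridement; stratifying it is a cheap gain if debridement strongly affects return to work

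*Protocol article*

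**What the plan says.** The Randomization section allocates patients 1:1 "with stratification by the need for debridement and randomly permuted block sizes from 2, 4, or 6". The Primary analysis section carries that factor into the MEPS comparison, "accounting for the debridement stratification variable and baseline MEPS", and names it again for the regression that estimates the treatment effect.

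The Secondary analysis section does not mention the factor. For return to work it plans Kaplan-Meier medians by arm, and "a statistical comparison between groups will be tested using a log rank test". The mean scores and grip strength "will be tested with ANOVAs and effect sizes estimated with linear regression", also with no stratum named. The text neither calls the log-rank test unstratified nor rules out a stratified version.

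Purpose and hypothesis lists return to work among the stated hypotheses, expecting it to favour the release. The Sample size calculation section powers MEPS only. It gives no hazard ratio, median, event count or power for return to work.

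**The concern.** Permuted blocks within strata force the arms to be nearly balanced on debridement. If debridement status also predicts when patients return to work, two things follow for a log-rank test that ignores it:

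- **Variance.** The variance the test uses still allows for chance imbalance on debridement, which the design has largely removed. The test statistic is then too small on average, and the true error rate falls below the nominal 5%.
- **Contrast.** Pooling fast and slow returners makes the overall hazard ratio smaller than the ratio within each stratum.

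Both reduce power. The protocol gives some reason to think the factor could matter. Background describes intra-articular pathology as a possible source of lasting pain after release. The strata also receive different procedures, since debrided patients get a true lateral working portal in either arm, while non-debrided sham patients get only a skin incision. At stake is the power of one hypothesis-bearing secondary comparison in a trial sized for another outcome.

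**Working it through.** **The plan's own figure.** The only sample size in the document is for MEPS: a "minimally clinically important difference of 15 points on the MEPS primary outcome measure", "assuming a standard deviation of 19 points as well as an alpha level of 0.05", with 80% power. With two-sided alpha, n per arm = 2 × (1.960 + 0.842)² × 19² / 15² = 25.2, so 26 per arm and 52 in total, as stated. With 5% unblinding and 15% loss, 26 / 0.80 = 32.5, or 33 per arm (66). Starting from 27 per arm, as an exact t calculation requires, 54 / 0.80 = 67.5 gives the stated 68. So 68 randomised patients, or about 54 evaluable (68 × 0.80 = 54.4), are the numbers available for return to work.

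**Inputs from the documents.** N = 68 or 54; stratified blocks of 2, 4 or 6; alpha 0.05; follow-up to 24 months; 28% debrided. The last is the synovitis debridement rate in one retrospective series cited in Background, not a trial assumption.

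**Assumptions the documents do not supply.** Treatment hazard ratio for return 2.0; exponential times with a 3-month median in non-debrided sham patients; debrided patients returning at 1/k of the non-debrided rate, with k from 1 to 5.

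**Benchmark.** With no stratum effect and every patient returning, power = Φ(√(D/4) × ln HR − 1.96). For D = 68 and HR = 2 this is Φ(4.123 × 0.693 − 1.96) = Φ(0.898) = 81.5%. For D = 54 it is 72.1%. The simulated plain test gives 79.0% and 68.2%, slightly below these, as expected in small samples.

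**Method.** At each event time, compare the observed number of returns d₁ in the release arm with its expectation d·n₁/n, and sum the differences to U and their hypergeometric variances to V. The test statistic is U²/V, compared with 3.84. The plain test uses one risk set. The stratified test computes U and V within each debridement stratum, adds them, and then forms (ΣU)²/ΣV. There were 4,000 trials per cell, so the Monte Carlo standard error is about 0.7 points for power and 0.35 for type I error.

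**Results, N = 68, 28% debrided (%):**

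| Stratum effect k | Power, plain | Power, stratified | Loss from plain test | Type I, plain | Type I, stratified |
|---|---|---|---|---|---|
| 1.0 | 79.0 | 77.9 | −1.1 | 5.5 | 5.2 |
| 1.5 | 77.9 | 77.6 | −0.3 | 5.4 | 5.4 |
| 2 | 74.8 | 78.1 | 3.3 | 4.4 | 5.4 |
| 3 | 64.5 | 77.8 | 13.3 | 3.2 | 5.1 |
| 5 | 49.3 | 76.1 | 26.8 | 1.7 | 5.6 |

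**Sensitivity (plain vs stratified power):**

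- N = 54, 28% debrided: 68.2 vs 66.1 at k = 1; 61.8 vs 66.6 at k = 2; 53.3 vs 66.5 at k = 3.
- N = 68, 50% debrided: 72.5 vs 76.4 at k = 2; 64.2 vs 77.5 at k = 3.
- N = 68, 28% debrided, return recorded only at the 3, 6, 12 and 24 month visits: 68.8 vs 73.1 at k = 2; 59.6 vs 72.2 at k = 3.
- A separate run with 54 patients, 15 of them debrided, and censoring at 12 months (3,000 trials per scenario): 59.6 vs 65.1 at k = 2; 50.6 vs 63.2 at k = 3.

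The pattern is the same throughout. Part of the gap reflects size: the stratified test sits slightly above 5%, at up to about 6% with 54 patients.

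**The case against.** The strongest objection is that the point rests on silence in a condensed article. The Secondary analysis section is brief throughout and leaves the stratum out of its ANOVAs too, so a reader should not infer a decision to drop it. An unseen SAP may already specify a stratified test. That stands as a limit on the claim. The article does name a test, however, and its immediately preceding section names the stratum, so aligning the two is a reasonable request.

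Nor do the documents show a strong stratum effect. The Background remark concerns pathology that is often missed, whereas here it is looked for and debrided before randomisation in both arms. This also stands: k = 3 or 5 is conjecture.

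The overall comparison is also a legitimate one. It tests the same marginal curves that the Kaplan-Meier medians summarise. So the choice concerns efficiency and consistency with the design, and neither test is wrong.

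A reader might infer that the plain test loses power whenever debridement affects recovery. The calculations do not support this, since no loss is detectable at a 1.5-fold effect. A reader might also infer that the planned comparison is invalid. It is not, because ignoring a balanced prognostic stratum pushes the error rate down.

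**Conclusion.** The point holds as a minor one. The return-to-work test as written does not carry the randomisation stratum that the primary analysis does. With an assumed treatment hazard ratio of 2.0 and 28% debrided, the cost is undetectable at a 1.5-fold stratum effect, about 3 to 5 points of power at 2-fold and about 12 to 14 at 3-fold. At 3-fold the plain test's type I error falls to about 3%. These figures depend on the assumed treatment effect, control median and stratum effect, none of which the documents give. The outcome is secondary with no power claim, any error is in the conservative direction, and the MEPS conclusion is untouched.

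**What to change.** State that return to work will be compared between arms with a log-rank test stratified by the debridement randomisation stratum, and that any Cox model used to report a hazard ratio will be stratified in the same way. Keep the Kaplan-Meier medians by arm. If the SAP already says this, nothing further is needed. Otherwise make the change before unblinded data are seen.

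The cost is one phrase and no new data, because debridement status is known for every randomised patient. If debridement is unrelated to return to work, the stratified test gives up about 1 to 2 points of power at 28% debrided (79.0% to 77.9% with 68 patients, 68.2% to 66.1% with 54).
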